## Abstract

**Background:**

Mild cognitive impairment (MCI) is a clinically important stage at which non-pharmacological interventions may help preserve cognitive function and daily functioning. Existing digital cognitive training programs are often limited by static task progression, declining engagement, and insufficient responsiveness to moment-to-moment cognitive and emotional states.

**Objective:**

This study protocol describes a single-center, parallel-group, assessor-blinded randomized controlled trial evaluating an adaptive cognitive training intervention delivered by a socially assistive robot and supported by a large language model (LLM).

**Methods and analysis:**

A total of 126 adults aged 60 years or older with MCI will be randomized 1:1 to either an LLM-supported robot-assisted adaptive cognitive training intervention (*n* = 63) or a matched non-adaptive computerized cognitive training control condition (*n* = 63). Both groups will receive three individually delivered sessions per week for 24 weeks, with each session lasting approximately 45–60 min, followed by a 12-week post-intervention follow-up to assess durability. The intervention group will receive multi-domain cognitive training through a socially assistive robot, with the LLM used as a bounded communication module that generates supportive language for controller-selected task adaptation, instruction style, feedback, and motivational support according to prespecified performance and affective indicators. The primary outcome is change in Montreal Cognitive Assessment (MoCA) score from baseline to week 24. Maintenance of cognitive change at week 36 will be analyzed as a secondary exploratory durability outcome. Secondary outcomes include domain-specific cognitive performance, emotional symptoms, motivation, engagement, adherence, usability, acceptance, expectancy and novelty effects, and safety. A nested exploratory imaging-biomarker sub-cohort will undergo resting-state functional magnetic resonance imaging and plasma biomarker assessment to explore changes in functional connectivity and neurobiological markers. Analyses will follow the intention-to-treat principle using mixed-effects models for repeated measures.

**Ethics and dissemination:**

The protocol has been approved by the Ethical Committee of the School of Nursing and Rehabilitation, Shandong University (Approval No. 2026-R-072; approved March 10, 2026). Written informed consent will be obtained before enrollment.

**Clinical Trial Registration:**

https://www.chictr.org.cn/historyversionpubEN.html?regno=ChiCTR2600125870, identifier ChiCTR2600125870.

## Introduction

Mild cognitive impairment (MCI) is a clinically meaningful intermediate state between expected cognitive aging and dementia. It is associated with measurable cognitive decline, elevated risk of functional deterioration, and increased likelihood of progression to Alzheimer disease or other dementias (1, 2). Because pharmacological options for MCI remain limited and disease-modifying treatment pathways are still evolving, non-pharmacological strategies such as cognitive training and cognitive stimulation remain central to early intervention research (3–5).

Computerized cognitive training can be scalable, repeatable, and relatively low risk, but clinical effects have been inconsistent. Several barriers are particularly relevant for older adults with MCI: static task sequences, limited personalization, low ecological validity, fatigue, and progressive decline in engagement during repeated training (4, 6, 7). These limitations suggest that digital cognitive interventions should not only deliver cognitive challenge but also respond to the user state during the session.

Socially assistive robots may improve the human-centered qualities of digital interventions by providing embodied interaction through speech, gaze, gesture, and affective cues. Prior work in geriatric care and rehabilitation suggests that robot-assisted systems can be acceptable to older adults and may support engagement, social presence, and motivation (8–10). However, many existing robot systems still rely on scripted or rule-based dialogue, which restricts their ability to support flexible conversation, sustained personalization, and affect-sensitive interaction across repeated sessions.

Recent progress in large language models (LLMs) provides a technical pathway for more context-aware and adaptive interaction in digital health interventions (11, 12). In parallel, the just-in-time adaptive intervention (JITAI) framework offers a behavioral science model for delivering support when and how it is needed, based on dynamically changing individual states (13). For clinical trials involving artificial intelligence, the SPIRIT-AI extension emphasizes transparent reporting of the AI intervention, input and output data, human-AI interaction, error handling, and version control (14). These reporting principles are especially relevant when an LLM is embedded in a health-related intervention for cognitively vulnerable participants.

This protocol describes a randomized controlled trial of an LLM-supported socially assistive robot for adaptive cognitive training in older adults with MCI. The intervention combines a cognitive adaptation loop, which adjusts task difficulty based on real-time performance, with an affective-motivational adaptation loop, which adjusts prompting and emotional support based on observed or inferred user state. The study aims to evaluate the clinical effect of the adaptive intervention compared with a matched non-adaptive active control condition and to explore potential neurobiological correlates through a nested imaging and fluid biomarker sub-cohort.

Beyond global cognition, older adults with MCI may also experience depressive symptoms, anxiety, apathy, and reduced initiative, which can influence adherence, motivation, and responsiveness to cognitive interventions (15–19). These symptoms are therefore relevant both as secondary outcomes and as user-state indicators for adaptive intervention delivery.

Evidence from lifestyle, cognitive training, and ecologically oriented rehabilitation research suggests that active, socially integrated, and multi-domain approaches may support cognitive performance and everyday functioning, although transfer effects and neural mechanisms remain incompletely understood (20–28). These considerations support the use of a multi-domain training program with engagement, functional relevance, and exploratory neurobiological outcomes built into the protocol.

## Methods and analysis

### Study design and setting

This is a prospective, single-center, parallel-group, assessor-blinded randomized controlled trial with a 1:1 allocation ratio. A total of 126 participants will be randomized, with 63 participants assigned to each group. Participants will be assigned to either an LLM-supported robot-assisted adaptive cognitive training group (AI-Robot group) or an active control group receiving non-adaptive computerized cognitive training. The intervention period will last 24 weeks, with assessments at baseline, immediately after completion of the intervention (week 24), and 12 weeks after intervention completion (week 36). A nested exploratory imaging-biomarker sub-cohort will undergo resting-state functional magnetic resonance imaging (rs-fMRI) and plasma biomarker testing at baseline and week 24.

The protocol has been structured to align with SPIRIT 2013 and the SPIRIT-AI extension for trial protocols involving artificial intelligence components (14, 29). The trial has been registered with the Chinese Clinical Trial Registry (ChiCTR; ChiCTR2600125870; prospective registration; https://www.chictr.org.cn/historyversionpubEN.html?regno=ChiCTR2600125870). The trial will be conducted at the Community Health Service Center of Baotuquan Subdistrict, Lixia District, Jinan, Shandong Province, China, and associated community-based research settings. Protocol version: Version 1.0, March 10, 2026. Study status at resubmission (July 2026): not yet recruiting. The conceptual workflow of the intervention is shown in Figure 1.

**Figure 1 F1:**
[figure not shown]
Conceptual workflow of the LLM-supported JITAI socially assistive robot cognitive training intervention. Task performance and behavioral-affective inputs are summarized into a structured user-state vector. A prespecified rule-based adaptive controller selects the tailoring action. The LLM communication module generates bounded supportive language only and cannot autonomously alter the selected action. The socially assistive robot delivers the controller-selected intervention. Parallel human safety oversight can override or de-escalate the controller and pause or stop robot delivery. The complete adaptive embodied package will be compared with a matched active control.

### Trial status

At the time of resubmission (July 2026), the trial had been prospectively registered but recruitment had not yet started. The planned overall study period is March 10, 2026, to June 30, 2028. Recruitment is expected to begin after resubmission and completion of the relevant approval procedures; the anticipated recruitment period has therefore been revised to September 1, 2026, to September 30, 2027, and the trial registry will be updated accordingly before enrollment begins. Each participant will be followed for 252 days, covering the 24-week intervention period, the week 24 post-intervention assessment, and the 12-week post-intervention durability follow-up at week 36.

### Objectives and hypotheses

The primary objective is to evaluate whether 24 weeks of LLM-supported robot-assisted adaptive cognitive training improves global cognitive function, measured by the MoCA, compared with a matched non-adaptive computerized cognitive training control condition.

Secondary objectives are to examine effects on domain-specific cognitive performance, emotional symptoms, motivation and engagement, intervention adherence, usability, acceptance, safety, and durability of cognitive effects at 12-week post-intervention follow-up. The exploratory mechanistic assessment will examine whether changes in cognitive outcomes are accompanied by changes in rs-fMRI connectivity involving the default mode network (DMN) and executive control network (CEN), and by changes in plasma biomarkers related to synaptic plasticity and neurodegeneration.

The main hypothesis is that participants in the AI-Robot group will show greater improvement in MoCA scores from baseline to week 24 than participants in the active control group. Exploratory hypotheses are that the AI-Robot group will demonstrate higher engagement, better adherence, fewer overload-related session interruptions, better maintenance of cognitive gains at week 36, and favorable changes in neural connectivity and biomarker profiles.

### Participants and recruitment

Participants will be older adults with clinically diagnosed MCI. Recruitment will be conducted at the Community Health Service Center of Baotuquan Subdistrict, Lixia District, Jinan, Shandong Province, China, and through affiliated community health and local aging-service networks. Recruitment has not yet started and is expected to begin after resubmission and completion of the relevant approval procedures. The anticipated recruitment period is September 1, 2026, to September 30, 2027. Potential participants will receive oral and written information about the study, and trained research staff will assess eligibility before obtaining written informed consent. Participants may withdraw at any time without affecting access to usual care or community services.

For participants with borderline decisional capacity, consent procedures will follow local ethical requirements. A family member or legally authorized representative may be involved when required by institutional policy, but participants will be included only when they can express willingness to take part in the study procedures.

### Eligibility criteria

Inclusion criteria are as follows:
Age 60 years or older.Meeting Petersen's diagnostic criteria for mild cognitive impairment based on clinical evaluation.MoCA score between 18 and 25 as a study-specific cognitive screening criterion after applying the original MoCA education correction (+1 point for participants with 12 years of education or fewer), with MCI confirmed clinically according to Petersen's criteria (1, 2, 30).Having sufficient language communication, hearing, and vision abilities to understand study instructions and complete assessments and training, with aids if needed.Living in a community or home setting and able to attend the 24-week cognitive training program as scheduled.Able and willing to provide written informed consent. Willingness and eligibility for MRI will be required only for the nested imaging-biomarker sub-cohort; refusal of MRI or MRI contraindication will not affect eligibility for the main randomized trial.The MoCA range of 18–25 is a study-specific eligibility threshold intended to enrich the sample for mild objective cognitive impairment while reducing inclusion of participants with probable normal cognition at the upper boundary or dementia-level impairment at the lower boundary; it is not used as a standalone diagnostic cutoff for MCI. For candidates scoring 24–25 after education correction, enrollment will require corroborating clinical evidence of cognitive concern and preserved basic activities of daily living consistent with MCI. The education-adjustment rule, raw score, adjusted score, education years, and clinical confirmation will be recorded in the screening log.

Exclusion criteria are as follows:
Diagnosis of Alzheimer disease dementia, other forms of dementia, delirium, or another condition that explains cognitive impairment better than MCI.Severe or unstable psychiatric disorder, neurological disorder, or medical illness that would interfere with participation or outcome assessment.Contraindications to MRI, such as implanted metallic devices or severe claustrophobia, for participants entering the imaging-biomarker sub-cohort.Severe sensory, speech, physical, or functional impairment preventing meaningful interaction with the robot or tablet-based training system.Participation in another cognitive intervention clinical trial during the study period.Any condition judged by investigators to pose excessive risk or compromise protocol adherence.

### Randomization and blinding

After eligibility confirmation and baseline assessment, eligible participants will be randomized to the AI-Robot group or active control group using a computer-generated block randomization sequence with a 1:1 allocation ratio. The allocation sequence will be generated by an independent researcher who is not involved in recruitment, intervention delivery, outcome assessment, or data analysis. Allocation concealment will be maintained using sequentially numbered, opaque, sealed envelopes until the participant has completed baseline assessment and has been formally enrolled.

Because of the nature of the intervention, participants and intervention facilitators cannot be blinded to group assignment. Outcome assessors, MRI analysts, laboratory staff, and statistical analysts will remain blinded to group allocation until the primary analysis has been completed. Participants will be reminded not to disclose group assignment to outcome assessors.

### Interventions

Both groups will receive three sessions per week for 24 consecutive weeks, for a maximum of 72 scheduled sessions. Each session will last approximately 45–60 min and will target multiple cognitive domains commonly affected in MCI, including episodic memory, attention, executive function, language, and orientation. Sessions will be delivered individually in a quiet room by trained facilitators who can assist with technical issues and monitor participant safety but will not provide additional cognitive coaching beyond the protocol.

Both arms are specified according to TIDieR and CONSORT guidance for non-pharmacological interventions, with equivalent reporting of provider, setting, dose, session structure, facilitator contact, permitted assistance, materials, and fidelity monitoring (31, 32). The intended contrast is the adaptive, embodied, LLM-supported tailoring component; therefore, schedule, contact time, target cognitive domains, basic facilitator presence, and visit environment will be matched as closely as feasible between groups.

### AI-Robot group: LLM-supported socially assistive adaptive cognitive training

Participants assigned to the AI-Robot group will receive cognitive training delivered by a socially assistive robot. The robot will provide spoken instructions, conversational prompts, task feedback, and session summaries. The intervention architecture comprises three layers: a robot/tablet front end for task delivery, a deterministic rule-based adaptive controller, and a version-locked Chinese-capable LLM communication module that generates supportive wording for controller-selected tailoring actions. The LLM will function as a constrained communication component within protocol-defined boundaries. It will not make diagnoses, provide medication advice, or replace clinical judgment.

Each session will follow a three-phase structure. The warm-up phase (approximately 5–10 min) will include brief social greeting, orientation questions, and low-demand cognitive activities. The core training phase (approximately 30–40 min) will include adaptive tasks targeting memory, attention, executive function, language, and orientation. The cool-down phase (approximately 5–10 min) will summarize performance, provide positive closure, and assess fatigue or distress.

Training tasks will be embedded in everyday scenarios, such as remembering appointments, following multistep instructions, semantic categorization, planning a daily schedule, and solving practical problems. Task complexity can be modified by adjusting the number of stimuli, memory load, rule complexity, interference, response-time expectations, and the amount of cueing provided.

At prespecified decision points, usually after each task block or every 5–10 min, the system will summarize task accuracy, median response latency relative to the task target, error patterns, repeated requests for help, hesitation, verbalized confusion, facilitator-rated fatigue or distress, and engagement indicators into a structured user-state vector. A deterministic rule layer will govern adaptation before any LLM-generated wording is delivered: difficulty may increase only when accuracy is at least 80% and median latency is no greater than the task-specific target for two consecutive blocks with no more than mild distress; difficulty is maintained when accuracy is 60%–79% or latency is within 100%–150% of target; and difficulty is decreased or instructions are simplified when accuracy is below 60%, latency exceeds 150% of target, two or more help requests occur in a block, or fatigue/frustration is rated moderate or higher. These thresholds are prespecified pragmatic starting rules derived from expert consensus and feasibility considerations before trial initiation; they are not treated as validated clinical cut-offs and will be documented in the intervention manual.

The adaptive logic will prioritize participant safety and sustained engagement. Affective cues will be coded on a 0–3 facilitator checklist (0 = absent, 1 = mild, 2 = moderate, 3 = severe) using observable indicators such as repeated negative verbalizations, facial or vocal signs of frustration, disengagement, and explicit fatigue. A rating of 2 will trigger de-escalation, supportive feedback, or a rest break; a rating of 3, a participant request to stop, persistent confusion despite simplification, fall risk, or facilitator concern will trigger session termination according to prespecified stop rules. The LLM can generate supportive language within these boundaries, but it cannot override rule-based de-escalation or stop decisions.

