### Active control group: non-adaptive computerized cognitive training

Participants assigned to the active control group will receive non-adaptive computerized cognitive training matched to the AI-Robot group in session frequency, approximate duration, visit setting, facilitator presence, and target cognitive domains. Control tasks will cover memory, attention, executive function, language, and orientation, with the same total planned dose of up to 72 sessions. The active control will be delivered on a tablet or computer using a standardized task library and scripted instructions. Facilitators may provide technical assistance, repeat standardized instructions, and monitor safety, but they will not provide individualized cognitive coaching or motivational dialogue beyond the control manual.

Instructions and feedback in the active control condition will be standardized and limited to neutral task guidance and correctness feedback. Task difficulty will follow a predefined progression schedule based on session number and task block rather than real-time performance or emotional state. The control condition will not include user-state vector generation, JITAI-based adaptation, LLM-generated dialogue, embodied robot social behaviors, or personalized emotional support. This design is intended to compare the complete adaptive embodied intervention package with a matched non-adaptive computerized control condition while aligning session dose, cognitive domains, visit environment, and facilitator contact as closely as feasible. Accordingly, the trial evaluates the package-level effect of adaptive embodied delivery supported by bounded LLM communication, rather than the isolated effect of the LLM component or the robot interface alone.

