Secondary emotional and motivational outcomes will include depressive symptoms measured by the Geriatric Depression Scale-15, anxiety symptoms measured by the Generalized Anxiety Disorder-7 scale, apathy measured by the Apathy Evaluation Scale, training motivation measured using the Intrinsic Motivation Inventory interest/enjoyment and effort/importance subscales or a locally validated equivalent, perceived engagement measured using the User Engagement Scale-Short Form plus session-level logs, technology acceptance using an older-adult digital health or robot acceptance questionnaire, usability measured by the System Usability Scale, and brief expectancy, novelty, and perceived social-presence items to help interpret potential expectancy and novelty effects. Behavioral engagement will also be captured through session attendance, completed tasks, time on task, response latency, help requests, rest breaks, and dropout.

Safety outcomes will include adverse events, serious adverse events, intervention-related distress, fatigue, falls or near falls during visits, clinically significant anxiety or frustration during sessions, and technical failures that affect participant safety or data integrity. All adverse events will be recorded, graded, and reviewed according to the approved study procedures.

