## Discussion

This protocol describes an adaptive cognitive training intervention that integrates embodied social interaction, LLM-supported dialogue, and JITAI-based state tailoring for older adults with MCI. The design addresses a key limitation of many existing digital cognitive interventions: the inability to respond to momentary cognitive load, frustration, fatigue, or disengagement. By using a socially assistive robot as the interaction interface, the intervention aims to make cognitive training more socially meaningful and ecologically acceptable for older adults.

A major methodological contribution is the explicit separation of adaptive mechanisms from general cognitive stimulation. The active control condition is matched on training frequency, session duration, facilitator attention, visit environment, and cognitive domains, while withholding real-time state monitoring, rule-based tailoring, bounded LLM communication, embodied robot social behaviors, and affective-motivational tailoring. This comparison should help estimate the added value of adaptive embodied interaction beyond non-specific exposure to digital training, although expectancy, novelty, and perceived social presence may still differ between groups and will be measured to support interpretation.

The protocol also incorporates AI-specific governance elements. LLM versioning, prompt standardization, safety filters, constrained output categories, latency fallback rules, human oversight, transcript audit, and error-case review are intended to improve transparency and reproducibility. These procedures are essential because LLM-based systems can generate plausible but inaccurate or inappropriate content if not constrained and monitored. In this trial, the LLM is therefore treated as a bounded intervention component rather than an autonomous clinical decision-maker.

The nested imaging and biomarker sub-cohort may provide exploratory evidence about possible neurobiological correlates of adaptive cognitive training. Changes in DMN and CEN connectivity may help evaluate whether behavioral improvements are accompanied by altered network organization. Plasma BDNF, p-tau181, and NfL may provide complementary information about synaptic plasticity and neurodegeneration-related processes, although biomarker changes over a 24-week period should be interpreted cautiously.

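### Scheduled in-session ratings of distress and fatigue are specified only for the AI-Robot arm, so the between-arm comparison of these soft safety outcomes is open to ascertainment bias

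*Protocol article*

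**What the plan says.** **AI-Robot arm** (Protocol article, section on the AI-Robot group). At decision points, usually after each task block or every 5–10 min, the system summarises "facilitator-rated fatigue or distress, and engagement indicators into a structured user-state vector". The scale is given: "Affective cues will be coded on a 0–3 facilitator checklist", from absent to severe. The ratings have consequences: "A rating of 2 will trigger de-escalation, supportive feedback, or a rest break", and a rating of 3 ends the session. The cool-down phase of each session must also "provide positive closure, and assess fatigue or distress".

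**Control arm** (Active control group section). "The control condition will not include user-state vector generation". Facilitators give technical help, repeat standard instructions and watch for safety. The Discussion describes the control as matched on dose, setting and contact "while withholding real-time state monitoring, rule-based tailoring, bounded LLM communication".

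**Outcomes that depend on the same signs.** The safety outcomes in Outcome measures include "intervention-related distress, fatigue, falls or near falls during visits, clinically significant anxiety or frustration during sessions". Statistical analysis makes safety outcomes one of the families with Benjamini-Hochberg control. Objectives and hypotheses expects the robot arm to show "fewer overload-related session interruptions", as an exploratory hypothesis.

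**Capture not restricted to one arm.** A trained facilitator attends each session and may pause or stop it (AI system governance). Rest breaks and session interruptions are recorded (Adherence, retention, and concomitant care). Adverse-event monitoring is continuous (Table 1). Facilitators are not blinded (Randomization and blinding).

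**The concern.** Mild or moderate fatigue, distress and frustration are recorded only if someone looks for them and grades them. One arm has a scheduled, graded prompt to look. The other has an unstructured watch by a facilitator who knows the allocation. With the same true frequency of these states, more would be expected to reach the record in the robot arm.

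Two conclusions are at stake. A tolerability comparison could show an excess in the robot arm that comes from closer observation. The hypothesised reduction in overload-related interruptions could be hidden, because calling an interruption overload-related needs information on the participant's state that only one arm has in structured form. Both errors run against the robot arm. Neither can be repaired in analysis, because observations never made in control sessions cannot be recovered.

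**Working it through.** **1. The two arms side by side**

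| Element | AI-Robot arm | Control arm |
|---|---|---|
| Facilitator at each session | yes | yes |
| Rest breaks and interruptions logged | yes | yes |
| Continuous adverse-event monitoring | yes | yes |
| 0–3 checklist | specified | not specified |
| Fatigue/distress input at decision points | specified | user-state vector excluded |
| End-of-session fatigue/distress check | specified | not specified |

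The shared rows cover events that announce themselves. The unshared rows cover graded states that must be looked for.

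**2. How unequal the planned looking is**

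Inputs: core phase 30–40 min; decision points every 5–10 min; at most 72 sessions.

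- Fewest per session: 30/10 = 3. Most: 40/5 = 8.
- Over 72 sessions: 3 × 72 = 216 to 8 × 72 = 576, plus up to 72 cool-down checks.
- Specified for controls: none.

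These are planned opportunities at full attendance, assuming a fresh rating at each decision point. They do not measure bias.

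**3. What unequal detection could do (illustration only)**

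The protocol gives no event rates and no detection probabilities, so all of these are assumed. Group size comes from the sample-size section, which reproduces: 1.6 points, SD 3.0, two-sided 0.05 and 80% power give 56 per group, and 56/(1 − 0.10) = 62.2, rounded up to 63.

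Let the true participant-level risk p be equal in both arms, with detection 0.90 in the robot arm and s in controls. Observed risks are 0.90p and s·p, so the observed risk ratio is 0.90/s with no true difference:

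- s = 0.75: 0.90/0.75 = 1.2
- s = 0.60: 0.90/0.60 = 1.5
- s = 0.45: 0.90/0.45 = 2.0

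The chance of an unadjusted p < 0.05 against the robot arm is Φ[(Δ − 1.96·SE₀)/SE₁], where Δ is the difference in observed risks, SE₀ its pooled and SE₁ its unpooled standard error, with 63 per group. Worked case, p = 0.4 and s = 0.60: observed risks 0.36 and 0.24; Δ = 0.12; SE₀ = √(2 × 0.30 × 0.70/63) = 0.0817; SE₁ = √((0.36 × 0.64 + 0.24 × 0.76)/63) = 0.0809; the result is Φ(−0.49) ≈ 0.31.

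| Assumed true risk | s = 0.75 | s = 0.60 | s = 0.45 |
|---|---|---|---|
| 0.2 | 7% | 15% | 31% |
| 0.4 | 11% | 31% | 63% |
| 0.6 | 17% | 53% | 88% |

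With equal detection the nominal figure in this direction is 2.5%. Benjamini-Hochberg adjustment would lower the tabled figures somewhat but would not remove the bias in the estimate.

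**4. Masking of a real benefit**

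With a true risk ratio of 0.5, the observed ratio is 0.5 × 0.90/s: 0.75 at s = 0.60 and 1.0 at s = 0.45.

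**5. Which outcomes are exposed**

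- Exposed: in-session distress, fatigue, anxiety and frustration, and the overload-related label on an interruption.
- Much less exposed: serious adverse events and falls.
- Not affected: MoCA, rated by blinded assessors.
- Mixed: counts of rests and terminations. Ratings trigger these in the robot arm, so a difference is partly a real effect of the package.

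**The case against.** The strongest reply is that the link from checklist to outcome is inferred. The protocol presents the ratings as inputs to the adaptive controller and stop rules. It says adverse events are recorded and graded under approved procedures that are not shown, and it sets a clinical-significance threshold for anxiety and frustration. This stands in part: a reader might infer that the checklist is the data source for the safety outcomes, and no section says so. The asymmetry still acts if safety events come from a separate form. The unblinded facilitator who is prompted to grade distress on a schedule is the person best placed to report it, and the control facilitator has no such prompt.

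Second, capture common to both arms is considerable, and the Interventions section promises equivalent reporting of session structure and fidelity monitoring. That stands for overt events. It does not supply controls with a structured rating, and the Discussion says real-time state monitoring is withheld. This is therefore a stated design feature and not detail left to a manual.

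Third, this is a package trial with state monitoring among the withheld components. It follows that monitoring cannot be treated as wholly outside the experimental contrast, and that rating-triggered rests and terminations belong partly to the package effect. But a package contrast does not require outcomes to be measured differently by arm. States can be recorded in controls without acting on task progression.

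Finally, a reader might infer that the whole safety comparison is uninterpretable, or that 216–576 ratings measure the distortion. The document supports neither: hard events are little exposed, and those figures count planned observations.

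**Conclusion.** The point holds for the soft in-session outcomes and for the classification of interruptions as overload-related. As written, the plan compares these between arms with a scheduled graded rating in one arm and none specified in the other, both observed by unblinded facilitators. The likely direction is more recorded events in the robot arm, which would create an apparent harm or hide the hypothesised benefit rather than manufacture a benefit.

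The size cannot be derived from the document. The illustrated risk ratios of 1.2 to 2.0 and false-signal chances of about 7% to 88% rest wholly on assumed risks and detection probabilities, and show only that modest differences in detection could matter with 63 per group.

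The primary MoCA analysis is not in question, and the remaining safety outcomes are not shown to be unreliable. This should be fixed as a matter of secondary and exploratory outcomes; it does not threaten the trial's main conclusion.

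**What to change.** Have the facilitators already present in both arms complete the same 0–3 checklist at matched time points and the same end-of-session fatigue/distress check. In the control arm, record these for outcome purposes only and do not feed them to task progression. Leave the existing facilitator provisions for pausing or ending a session unchanged.

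Define in-session distress, fatigue, anxiety and frustration, and an overload-related interruption, from this common form and in the same words for both arms. Report counts of rests and terminations separately, noting that in the robot arm some are triggered by the ratings and so are part of the package.

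If the common form is not adopted, report these soft comparisons as descriptive and take them out of the tested safety family.

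The cost is one form, some wording in the control manual, a little facilitator time and slightly more structured observation in the control arm, which narrows the contrast a little. Recruitment has not begun and the intervention manual is still to be locked, so the change can be made before any data are lost.
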